## **9.2 Sample Size: (IRAS A59, A60)**

The sample size for this study has been calculated to determine whether maternal cardiac output (the primary outcome measure) decreases in the prone position compared to left lateral position. Milsom et al. demonstrated a mean cardiac output of 6.6L/min in left lateral position, 5.9L/min in right lateral position and 5.5L/min in a supine position and there was a standard deviation of 1.0L/min [1]. To have 80% power to detect a fall from the level reported for left lateral position (6.6 L/min) to 5.7 L/min (the midpoint between right lateral and supine positions) 20 participants would be required in each group using  $\alpha=0.05$ .

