#### **5) STUDY DESIGN & PROTOCOL**

##### **5.1 Participants (IRAS A15)**

We will conduct a cohort study of women with a viable singleton pregnancy over 28 weeks' gestation.

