## **9) STATISTICAL CONSIDERATIONS**

### **9.1 Statistical Analysis (IRAS A56, A62)**

Data regarding maternal characteristics will be analysed using descriptive statistics. Data regarding maternal cardiac output in different maternal positions will initially be evaluated to determine whether values are normally distributed. Depending on the distribution of values, they will be transformed to a normal distribution if appropriate and a repeated measures ANOVA performed. If they are not normally distributed and transformation does not achieve a normal distribution a Friedman test will be performed. This approach will address variation between individual participants.

Descriptive and comparative statistical analysis will be conducted in STATA (STATACORP, TX, USA). As the investigators anticipate some variation in the baseline observations between participants both raw values and change from baseline status will be evaluated.

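### The sample size of 20 in each group matches a formula for two independent groups, but the study is one cohort with a within-woman comparison, so the stated N and power do not describe it

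*Protocol*

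**What the plan says.** Protocol section 9.2 sets the sample size to find out "whether maternal cardiac output (the primary outcome measure) decreases in the prone position compared to left lateral position". It cites a published "mean cardiac output of 6.6L/min in left lateral position", takes 5.7 L/min as the target (midway between the cited right lateral and supine values of 5.9 and 5.5), and adds that "there was a standard deviation of 1.0L/min". With 80% power and an alpha of 0.05 (one- or two-sided is not stated), it concludes that "20 participants would be required in each group".

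The rest of the protocol describes a single group. Section 5.1 says "We will conduct a cohort study of women with a viable singleton pregnancy over 28 weeks' gestation". Under section 5.2 every woman lies on her left side for 20 minutes, then prone on the cushion for 30 minutes, then on her left side again for 20 minutes. Section 9.1 plans a repeated measures ANOVA, or a Friedman test if normality cannot be achieved, and says of this: "This approach will address variation between individual participants". It also plans to look at change from baseline. No section defines a second group or states a total number of women.

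**The concern.** In a within-woman comparison, the precision of the mean change depends on the SD of the prone minus left-lateral difference. That in turn depends on how strongly a woman's two values are correlated. Section 9.2 gives neither quantity. It gives one SD beside the position means and an N per group, which are the inputs and output of a calculation for two separate sets of women.

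Two things are at stake. First, the recruitment target has two readings: 20 women, each measured in both positions, or 40 women. Second, the 80% power for a 0.9 L/min fall is not this study's power. Anyone interpreting a null result on a question of maternal safety needs to know what fall the study could have found.

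**Working it through.** **Inputs, all from section 9.2.** Left-lateral mean 6.6 L/min; target 5.7 L/min, so the fall is 6.6 − 5.7 = 0.9 L/min; SD 1.0 L/min; power 80%; alpha 0.05.

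**Step 1: reproduce the stated figure.** For two independent groups, two-sided, by normal approximation:

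n per group = 2 × (1.960 + 0.842)² × 1.0² / 0.9² = 19.38, rounded up to 20.

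This matches. Variants do not:
- A one-sided version gives 16 per group.
- A two-sample t-test gives 21 per group (power at 20 per group is 79.2%).
- A paired t-test that reads 1.0 as the SD of the differences gives 12 women; its normal approximation is 9.69, so 10.

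The protocol does not name its formula. That it is the independent-groups formula is inferred from the match and from the words about each group.

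**Step 2: set up the calculation for the planned design.** Assume SD 1.0 L/min in each position, one summary value per woman and position, and a paired two-sided 5% t-test (noncentral t). With within-woman correlation rho:

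SD of difference = 1.0 × √(2 × (1 − rho)).

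The protocol gives no rho, so a range is shown.

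| rho (assumed) | SD of difference (L/min) | Women for 80% power, fall of 0.9 | Power with 20 women, fall of 0.9 | Fall detectable with 80% power, 20 women (L/min) |
|---|---|---|---|---|
| 0 | 1.41 | 22 | 77% | 0.93 |
| 0.3 | 1.18 | 16 | 90% | 0.78 |
| 0.5 | 1.00 | 12 | 97% | 0.66 |
| 0.7 | 0.77 | 8 | 99.8% | 0.51 |

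**Step 3: find where 20 women stop being enough.** Power with 20 women is exactly 80% when the SD of the difference is 1.36 L/min. Solving 1.36 = √(2 × (1 − rho)) gives rho = 1 − 1.36²/2, or about 0.07. Below that correlation, power is under 80%.

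**Step 4: the other reading of N.** With 40 women, each measured in both positions, power for 0.9 L/min is 97.5% at rho 0 and above 99.9% at rho 0.5.

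The repeated 5-minute readings would change the variance of each woman's summary value. The protocol gives no figures for this, so it is left out.

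**The case against.** The best defence is that an independent-groups formula is a common and cautious stand-in when no SD of within-woman change is to hand. Ignoring a positive correlation overstates the number needed. The words about each group may simply mean each position, so that 20 women in total are intended. By normal approximation, a paired calculation with rho set to 0 is algebraically the same and also gives 20. The primary objective in section 4.1 is moreover to describe effects, so the exact power matters less than in a confirmatory trial.

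Much of this stands. Cardiac output measured in the same woman within about an hour is unlikely to be uncorrelated, and section 9.1 itself expects women to differ at baseline. But section 9.2 does not say that it is a cautious approximation, does not say that group means position, and does pose a comparative question with a stated power.

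Three stronger readings are tempting, and the documents do not support them:
- *The study is underpowered.* With 20 women this is so only if rho is below about 0.07, and even at rho 0 power is 77%.
- *The plan does not say what it can detect.* It does: a fall from 6.6 to 5.7 L/min. The fault is that the power attached to that fall comes from a different design.
- *The recruitment rate sets a third target.* Section 7 expects two participants a week for six months, roughly 2 × 26 = 52 women. That describes duration and pace, and is not a sample size.

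**Conclusion.** The point holds as a mismatch between design and formula. The arithmetic is right for the formula used, but the formula is not the one for this study. The stated 20 in each group with 80% power is therefore not a property of the design, and the total number of women can be read as 20 or 40.

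The consequence is modest and probably on the safe side. For rho between 0.3 and 0.7, the 20-woman reading has 90% to 99.8% power for 0.9 L/min, and 80% power for falls of 0.78 down to 0.51 L/min. These figures rest on SD 1.0 L/min in both positions, one value per woman and position, a paired two-sided 5% t-test, and correlations that are this review's assumption. The correction should be made, but nothing here shows that the study would fail or that its analysis is wrong.

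**What to change.** Rewrite section 9.2 as a paired comparison in one cohort:

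- Remove the reference to each group and state one total number of women.
- State the assumed SD of the within-woman prone minus left-lateral difference, or SD 1.0 L/min per position with a correlation and a range around it.
- State that the test is two-sided, and give the power or the detectable fall for that total.

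For example: 20 women in total give about 97% power for a fall of 0.9 L/min, or 80% power for a fall of about 0.66 L/min, if the correlation is 0.5; at correlations of 0.3 and 0.7 the power for 0.9 L/min is 90% and 99.8%.

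The cost is protocol wording, plus a correlation or SD of change that the investigators must choose and defend. At plausible correlations no extra women are needed.

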## **10) DATA MONITORING AND QUALITY ASSURANCE (IRAS A74, A75-1)**

The study will be subject to the audit and monitoring regime of the University of Manchester. The investigators / institutions will facilitate study-related monitoring, audits, review by independent ethics committee and regulatory inspections providing direct access to source data / documents to authorised study or regulatory personnel.

## **11) SAFETY CONSIDERATIONS AND ADVERSE EVENTS (IRAS A75-1, A75-2)**

Prior studies suggest that lying prone does not have adverse consequences for mother or baby. However, it is possible that a mother may develop symptoms, have deviations from blood pressure or that the fetal heart rate trace would become abnormal. If these situations develop during the experimental protocol the procedure would be stopped and the mother transferred to a left-lateral position to allow a period for the abnormal symptoms or observations to resolve. The mother would be clinically assessed by the research midwife, if symptoms or abnormal observations do not resolve the mother would be transferred to the maternity department at St Mary's Hospital for further management. A handover would be given to the clinical staff by the research midwife looking after the participant. The need to terminate the protocol would be recorded in the study and reported in the final analysis.

## **12) PEER REVIEW (IRAS A54-1)**

This protocol has been peer-reviewed within the investigators institution by members with existing expertise on measurement of cardiac output and haemodynamic indices during pregnancy. Statistical input has been sought from [name], Maternal and Fetal Health Research Centre.

## **13) ETHICAL and REGULATORY CONSIDERATIONS**

### **13.1 Approvals**

Health Research Authority approval will be obtained before commencing research processes. The Medicines and Health Regulatory Agency have confirmed that the Anna Pillow does not need a CE mark to be used in practice or research as it is primarily concerned with comfort or pain relief.

The study will be conducted in full conformance with all relevant legal requirements and the principles of the Declaration of Helsinki, Good Clinical Practice (GCP) and the UK Policy Framework for Health and Social Care Research 2017.

### **13.2 Risks (IRAS A22 and A26)**

There is no risk to researchers, local health and safety SOPs will be followed at the Manchester Maternal and Fetal Health Research Centre.

### **14) STATEMENT OF INDEMNITY (IRAS A76-1,-2,-3, A77)**

The University has insurance available in respect of research involving human subjects that provides cover for legal liabilities arising from its actions or those of its staff or supervised students. The University also has insurance available that provides compensation for non-negligent harm to research subjects occasioned in circumstances that are under the control of the University.

### **15) FUNDING and RESOURCES (IRAS A65)**

The investigators have prepared applications to several charitable organisations (including the Dowager Countess Eleanor Peel Trust and the Sir Halley Stewart Research Trust). The results of these applications are awaited.

### **16) PUBLICATION POLICY (IRAS A50-1 – A53)**

After Research Ethics Committee and HRA approval has been obtained this protocol will be registered on [www.clinicaltrials.gov](http://www.clinicaltrials.gov). The investigators will disseminate the results of this study at appropriate national and international scientific meetings such as the British Maternal Fetal Medicine Society. Primary responsibility for preparing publications will lie with the Chief Investigator, [name]. To safeguard the integrity of the study, data from the study will not be presented in public before the main results are published without the prior consent of the co-investigators. Acknowledgements will include the trial staff at the study site.

